###### Working memory

2.4.4.1.2

An adapted version of the digit memory test will be used to measure the working memory (Hill et al., 2010). Students will listen to digit sequences and write them down (i.e., 1, 4, 6). If successful, longer sequences will be given until two consecutive failures occur. One researcher dictates while another oversees. This test includes: “Digits Forward,” where participants write the digits in the given order, and “Backward Digit-Span,” where participants write the digits in reverse order.

###### Cognitive flexibility

2.4.4.1.3

An adapted version of the Trail-making test (TMT) will be used to assess cognitive flexibility (Howie et al., 2015). The TMT will comprise two parts: (a) TMT-A will evaluate processing speed and visual attention, requiring participants to connect numbers from 1 to 25 in order; (b) TMT-B will assess cognitive flexibility by alternating between numbers and letters in ascending and alphabetical order. Students will record completion times using a digital stopwatch displayed on a screen. The test will be supervised by the two researchers. For the Trail Making Test (TMT) used with children, Cronbach’s alpha generally falls within 0.60–0.80 for its subtests, reflecting moderate reliability.

####### Selective attention

2.4.4.1.3.1

The d2, test of attention will be used to assess the selective attention (Brickenkamp, 2012). Students must carefully scan each of the 14 lines of the test from left to right, identifying any “d” with two small lines. These are considered relevant elements, while other combinations are irrelevant. Each line allows 20 s for assessment, with one researcher monitoring time and another ensuring the process runs smoothly. For the d2 in children, Cronbach’s alpha values are generally reported to be between 0.75 and 0.90, indicating strong internal consistency.

##### Secondary outcome measures

2.4.4.2

###### Academic performance

2.4.4.2.1

The academic fluency index and their subtests will be assessed similarly to phase I of the study (Muñoz-Sandoval et al., 2005). However, the procedure will vary. In this instance, all students within a specific classroom will undertake the tests simultaneously, with two trained researchers overseeing to ensure that each student completes it independently (time will be monitored using a chronometer).

###### Design and feasibility of active breaks

2.4.4.2.2

The responses collected from semi-structured interviews with teachers and school staff, along with the semi-structured questionnaires administered to students, will be instrumental in shaping the design and assessing the feasibility of implementing active breaks. These tools will be rigorously validated through a Delphi methodology, involving a panel of at least 10 experts (Gillis et al., 2013). The questions will be developed using the RE-AIM framework and further refined according to the guidelines provided by Daly-Smith et al. (2021).

###### Physical activity and sedentarism

2.4.4.2.3

PA and sedentarism will be calculated by accelerometry (ActiGraph wGT3x-BT), using the same instrument and procedure in phase I (Migueles et al., 2017). Due to the limited availability of accelerometers, one accelerometer will be assigned to each classroom. This accelerometer will rotate among students daily (24-h) until each student has had a turn, being the classroom teacher responsible for its safekeeping. The classroom teacher will keep track of who will wear the accelerometer every day. Moreover, a researcher will handle data retrieval and recharge the battery once a week.

###### Intensity of the active breaks

2.4.4.2.4

Intensity of the active breaks will be measured by accelerometry (Migueles et al., 2017). Following the procedure of the above section, intensity of the active breaks will be measured. For this reason, the classroom teacher will receive a sheet to note at which time (hours: minutes: seconds) started and finished every active break.

###### Self-report of physical activity patterns

2.4.4.2.5

An adapted Spanish version of the PA questionnaire for children (PAQ-C) will be administered to evaluate PA patterns (Manchola-González et al., 2017). This self-administered questionnaire employs a seven-day recall period, comprising nine items measured on a 5-point Likert scale. For the PAQ-C, Cronbach’s alpha generally ranges from 0.70 to 0.85, reflecting good internal consistency.

###### Self-report of sedentarism

2.4.4.2.6

Sedentary patterns will be calculated using the same instrument and procedure (although, in this case, the evaluation will take place within a classroom setting) as in phase I (Segura-Díaz et al., 2021).

###### Sleep quality

2.4.4.2.7

Following the established procedure for measuring PA and sedentary patterns, sleep quality will be assessed using accelerometry (ActiGraph wGT3x-BT).

###### Self-report of physical fitness

2.4.4.2.8

Physical fitness will be measured through the adapted Spanish version of the International Fitness Scale (Sánchez-López et al., 2015). This instrument is composed of five items on a 5-point Likert scale. The Cronbach’s alpha of the International Fitness Scale in children, is generally reported to be between 0.70 and 0.85, indicating good internal consistency.

###### Self-report of body composition

2.4.4.2.9

The height (cm) and weight (kg) of the students will be self-reported by parents, which is a reliable alternative to direct measurements (Rios-Leyvraz et al., 2022). Then, BMI will be also calculated (kg/m^2^).

###### Students’ classroom behavior

2.4.4.2.10

Classroom teachers will employ two parts (inattention and hyperactivity-impulsivity) of the Child and Adolescent Behavior Inventory (CABI). Each of these parts is composed of nine items and uses a 6-point Likert scale (Burns et al., 2023).

###### Creativity

2.4.4.2.11

An adaptation of the Alternative uses task (AUT) will be used to measure creativity (Olson et al., 2021). Students will be required to complete the maximum number of unusual uses for two objects within a 3-min timeframe (with one researcher overseeing the timing and another guaranteeing of the process).

##### Confounding variables

2.4.4.3

The socioeconomic status of the children will be assessed using the validated Family Affluence Scale (FAS-II), which consists of four items specifically designed to measure socioeconomic status (Boyce et al., 2006). Additionally, self-reported body composition and self-reported PA patterns will also be considered as confounding variables in the analysis.

#### Implementation strategies and cost-effectiveness analyses

2.4.5

To guarantee the correct development of the intervention, a few implementation strategies will be conducted during the intervention period providing professional training for teachers (i.e., initial meeting before the start of the intervention); offering direct support from researchers (i.e., weekly visit at the school, and direct contact by e-mail or WhatsApp); granting access to the Break4Brain website for administering active breaks; and ensuring fidelity and follow-up of the active breaks (i.e., recording one active break weekly, and documenting daily participation of students).

Concerning the cost-effectiveness analyses, trial costs, and outcomes will be extrapolated to the Spanish population aged 10–12 in government schools, to assess the potential lifetime health and cost outcomes resulting from the intervention (Brown et al., 2024). The cost-effectiveness model will be determined using the validated ACE-Obesity Policy model (Ananthapavan et al., 2020).

#### Data analysis

2.4.6

##### Quantitative analysis

2.4.6.1

The outcomes will be analyzed utilizing linear mixed models in IBM SPSS Statistics for Windows, V.20.0 (IBM, Armonk, New York, USA), with significance levels set at *p* < 0.05. These models will evaluate the effects of the condition (video-based PA program and control group), time (pre and posttest), and the interaction between condition and time. Random effects will be incorporated to address the nested nature of the data, adjusting for clustering effects at the school level. Additionally, baseline PA levels, obesity status, gender, and age will be considered as potential moderators in the analysis. Moreover, all assumptions will be tested, and analyses will be adjusted for control variables if necessary.

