#### Sample size and power

2.4.1

A between subjects, 2 conditions (video-based PA program, and control condition) × 2 times (pretest vs. posttest) repeated measures ANOVA design with 138 participants should be sufficiently powered to detect interactions at or above moderate effect sizes *f* = 0.25 which translates to an approximate Cohen’s *d* = 0.5 assuming alpha at 0.05, power at 80%, and a correlation among 2 repeated measures of 0.75. Considering these estimations, and a potential dropout rate of 10% observed in similar studies (Mora-Gonzalez et al., 2019), our investigation will recruit 600 participants.

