**Figure 3 fig3:**
[figure not shown]
Flow diagram of the participant’s recruitment process.

Randomization of schools into experimental conditions for phase II is carried out using R software by an external statistician.

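### Phase II tests condition × time with unspecified random effects; fitted as school and pupil intercepts, the test would ignore clustering of change by school

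*Protocol article*

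**What the plan says.** Section 2.4.2 makes the school the unit of randomisation: "Randomization of schools into experimental conditions for phase II is carried out using R software by an external statistician". Section 2.4.6.1 (Quantitative analysis) specifies linear mixed models "with significance levels set at *p* < 0.05". The terms are condition, "time (pre and posttest), and the interaction between condition and time". With two arms and two waves, that interaction is the treatment effect. Clustering is covered by one sentence: "Random effects will be incorporated to address the nested nature of the data, adjusting for clustering effects at the school level". The section does not say whether the school effect is an intercept, a school-by-time effect or both, and it names no pupil or class effect.

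Section 2.4.1 sizes Phase II as a "repeated measures ANOVA design with 138 participants should be sufficiently powered to detect interactions at or above moderate effect sizes", with "a correlation among 2 repeated measures of 0.75". It uses no ICC and no design effect. The text gives no number of schools; the figures were not available for this review.

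**The concern.** In a school-randomised trial, the right error for a pre-post contrast between arms is the variation between schools in how much pupils change. A stable difference between schools is the same at both waves, so a school intercept absorbs it without touching the contrast. A model can therefore appear to adjust for school and still test the interaction against pupil-level error with hundreds of degrees of freedom.

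The design makes some clustering of change likely. Digit sequences are dictated by a researcher, trail-making times are read from a displayed stopwatch, and d2 lines are timed by a researcher (2.4.4.1.2, 2.4.4.1.3 and 2.4.4.1.3.1). The academic tests are taken by a whole class at once (2.4.4.2.1). Session effects of this kind differ between waves and are shared by classmates even when the programme does nothing. In the intervention arm, the class teacher also runs the breaks and chooses their time (2.4.3.1). At stake is the false-positive rate, or in one variant the power, of the Phase II outcome tests, including the three primary cognitive outcomes.

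**Working it through.** **The plan's own figures.** The nominal level is 0.05. The stated 138 pupils cannot serve as a benchmark for it. With f = 0.25, two groups, two times and r = 0.75, the between-group noncentrality is 0.0625 × 138 × 2 / 1.75 = 9.86 (power 0.876; 112 pupils give 80%). For the interaction it is 0.0625 × 138 × 2 / 0.25 = 69 (power above 0.999; 18 pupils give 80%). The 138 matches a between-group test with three groups (power 0.800). That is a separate matter and does not affect what follows.

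**Inputs.** From the article: 600 pupils, 300 per arm, two waves, r = 0.75, two-sided 0.05 (sidedness assumed). Assumed: 6 to 24 equal schools, so m = 100 to 25 pupils each, and an ICC of change ρ_D from 0 to 0.10.

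**Algebra.** Write each score as fixed effects + school u_j + pupil p_ij + school-by-time s_jt + residual e_ijt. The change is D_ij = (s_j2 − s_j1) + (e_ij2 − e_ij1) plus fixed effects; u_j and p_ij are gone.
- True variance of the arm difference in mean change: (4σ_D²/N) × [1 + (m − 1)ρ_D].
- Variance used by a model with school and pupil intercepts: 4σ_D²/N.
- Type I error, large-sample: 2{1 − Φ(1.96/√DE)}, with DE = 1 + (m − 1)ρ_D.

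Example, 12 schools of 50 and ρ_D = 0.05: DE = 1 + 49 × 0.05 = 3.45; 1.96/√3.45 = 1.055; type I error 0.291.

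**Check by mixed-model fit.** Three simulated trials (12 schools of 50, ρ_D = 0.05) had the stable school ICC set to 0, 0.05 and 0.20. The interaction SE with school and pupil intercepts was 0.0563, 0.0597 and 0.0589, equal to the pupil-level change-score SE each time. The school-level SEs were 0.098, 0.117 and 0.118.

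**Simulated type I error** (4,000 runs per row; Monte Carlo SE about 0.003 at 0.05). A = school and pupil intercepts; B = school intercept only; C = school-level change, equivalent to a school-by-time effect, on K − 2 df for K schools.

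| Schools × pupils | ρ_D | DE | A, formula | A | B | C |
|---|---|---|---|---|---|---|
| 24 × 25 | 0.01 | 1.24 | 0.078 | 0.080 | 0.001 | 0.046 |
| 12 × 50 | 0.01 | 1.49 | 0.108 | 0.099 | 0.002 | 0.043 |
| 8 × 75 | 0.01 | 1.74 | 0.137 | 0.140 | 0.006 | 0.048 |
| 6 × 100 | 0.01 | 1.99 | 0.165 | 0.162 | 0.007 | 0.043 |
| 24 × 25 | 0.05 | 2.20 | 0.186 | 0.179 | 0.010 | 0.045 |
| 12 × 50 | 0.05 | 3.45 | 0.291 | 0.301 | 0.043 | 0.058 |
| 8 × 75 | 0.05 | 4.70 | 0.366 | 0.375 | 0.076 | 0.050 |
| 6 × 100 | 0.05 | 5.95 | 0.422 | 0.422 | 0.119 | 0.055 |

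At ρ_D = 0, A gives 0.047–0.055. At 0.10, A gives 0.29–0.57.

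**Why B differs.** Without a pupil effect, pupil variance stays in the residual. With total variance 1 the model uses about 8/N, whereas independent pupils would give 4 × 2(1 − 0.75)/N = 2/N. The fourfold excess keeps the test conservative until DE passes about 4.

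**What ρ_D means in ordinary terms.** If a share v of total variance is school-by-time, ρ_D = 2v / [2(1 − 0.75)] = 4v. So ρ_D = 0.01 needs v = 0.0025 and ρ_D = 0.05 needs v = 0.0125. For example, an ICC of 0.05 with a school-level pre-post correlation of 0.8 gives v = 0.05 × 0.2 = 0.01 and ρ_D = 0.04. After 10% dropout (12 schools of 45), DE = 1 + 44 × 0.04 = 2.76 and type I error is about 24% by formula (22.9% simulated).

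**ANCOVA against change, independent pupils.** (1 − r²) / [2(1 − r)] = 0.4375/0.5 = (1 + r)/2 = 0.875.

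**The case against.** A reader might infer that the article commits itself to an intercept-only model, so that its test is invalid and its standard errors are too small for every primary outcome. The text does not support that. It never says random intercept, it speaks of random effects in the plural, and a school-by-time effect fits its wording. The direction of error is not fixed either: a school intercept with no pupil effect usually errs the other way, and with no clustering of change the two-intercept model is valid. The percentages belong to assumed school numbers and ICCs, not to this trial's data. A condition × time mixed model is also a legitimate analysis, so the ANCOVA gain alone shows no error.

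All of that stands. It is also fair to say that covariance structure and degrees of freedom are commonly left to an analysis plan. What remains is that the article does fix the tested contrast and does name the level of adjustment. Of the three models checked, all compatible with its wording, one inflates type I error, one is usually too conservative and one holds 5%. Nothing in the article points to the third, and a common way of fitting such a sentence is the first.

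**Conclusion.** The concern holds conditionally. As worded, Section 2.4.6.1 protects the Phase II test only if the fitted model carries school-level variation in change and its degrees of freedom reflect the number of schools. The inflation under two intercepts needs three things together: a pupil effect or equivalent, no school-by-time effect, and non-zero clustering of change. The third is likely from the shared testing sessions, but the article gives no figure for it. Its size is illustrative: smaller if there are many small schools, and nil if change does not cluster. The algebra itself is not in doubt.

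**What to change.** Make the main Phase II analysis an ANCOVA: post-test score on condition and baseline score, with a random intercept for school (and for class within school) and Satterthwaite or Kenward-Roger degrees of freedom. Here the school intercept does carry the relevant variation, because the outcome is a single wave. The baseline is already collected, and adjusting for it gains precision over the change contrast (factor 0.875 at r = 0.75 for independent pupils; the gain with clustering was not computed).

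If the two-wave model is kept, state pupil and school-by-time random effects with the same degrees-of-freedom correction.

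The cost is wording, settled before the data are analysed. Confidence intervals may be wider than under the intercept-only model, and it must be confirmed that the named software (SPSS version 20) supports the chosen degrees-of-freedom method.

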##### Qualitative analysis

2.4.6.2

Qualitative data will be gathered through semi-structured interviews and questionnaires administered by trained researchers. Thematic analysis techniques and a grounded theory approach will organize and manage all essential information obtained from the interviews. Quantitative data of the semi-structured questionnaire will be summarized into means and standard deviations. Semi-structured interviews will be audio-recorded, transcribed verbatim, and anonymized before coding. The analysis will be conducted using “NVivo version 12 Plus” software (QRS International-Melbourne, Australia).

## Discussion

3

The main objective of the Break4Brain Project is to examine the acute and chronic effects of PA (either with or without cognitive engagement) on academic performance, cognitive function, and brain function in ADHD-diagnosed and non-diagnosed children, in controlled laboratory settings and schools.

Recently, there has been a surge in studies evaluating the impact of active breaks on various educational outcomes in children (Watson et al., 2017; Daly-Smith et al., 2018). A predominant focus of these studies has been on investigating the effects of PA specifically on children without neurodevelopmental disorders. A strength of this study is that it will compare the findings of children with and without ADHD. Thus, an exploration into this area is warranted to elucidate potential variations in response to acute PA, ultimately facilitating the development of more tailored and effective interventions (in parameters of duration, intensity, or PA type) in both populations.

Despite numerous investigations into the effects of PA in children with ADHD, the precise impact on brain function, cognition, and academic performance remains elusive (Chan et al., 2022; Welsch et al., 2021). Current research has primarily focused on specific outcomes or short-term effects, often neglecting a holistic approach that includes a comprehensive battery of tests to assess these variables simultaneously. To the best of our knowledge, there is a significant gap in research that thoroughly examines the effects of acute PA on both brain function and academic performance in children with ADHD, particularly in comparison to their non-ADHD peers. This gap is especially critical given that children with ADHD may exhibit unique responses to PA interventions due to their distinct neurocognitive and behavioral characteristics. These differences suggest that PA might influence ADHD and non-ADHD children in divergent ways, potentially offering specialized benefits or necessitating tailored intervention strategies to maximize effectiveness. For example, a meta-analysis by Li et al. (2023) found that cognitively engaging exercises are particularly effective in improving attention problems in school-aged children with ADHD. This highlights the possibility that specific types of PA, especially those that engage cognitive processes, could be more beneficial for children with ADHD compared to their non-ADHD counterparts.

Regarding school settings, there has often been a disconnect between research evidence and the practical implementation of past interventions (McMullen et al., 2014). For instance, while existing evidence suggests certain strategies might be effective, qualitative feedback from educators reveals differing preferences. Teachers, for example, have consistently expressed a preference for short, video-based PA breaks lasting less than 10 min. This highlights the importance of aligning research with the practical realities and preferences within educational settings to enhance both feasibility and effectiveness. To address this challenge, our cluster RCT will be collaboratively designed with input from educational stakeholders, ensuring that the strategies are not only evidence-based but also practical, sustainable, and aligned with the day-to-day demands of teachers and students. This collaborative approach is crucial for the successful integration of active breaks into the school routine, as it fosters a sense of ownership and relevance among educators, which in turn, increases the likelihood of long-term adoption and sustainability. Moreover, the Break4Brain project’s digital platform significantly alleviates the workload for teachers by providing pre-designed, video-based PA breaks. These videos include clear, step-by-step instructions, allowing teachers to easily implement the activity by simply selecting the appropriate video. This system minimizes the preparation required by teachers and seamlessly integrates PA into the classroom environment without disrupting the flow of the school day. In this sense, and to our knowledge, this is the most comprehensive study in the field of active breaks, as it not only incorporates rigorous research methodologies but also addresses the practical needs of educators through a hybrid type 1 implementation-effectiveness trial. This approach ensures that the interventions are both effective in improving student outcomes and feasible for long-term implementation in real-world educational settings, bridging the gap between research and practice in a meaningful way.

Another strength of this study is that it will measure the fidelity of each student (and class) to the intervention. A recent systematic review and meta-analysis revealed that most published studies have failed to assess fidelity to active breaks (Ruhland and Lange, 2021). This underscores the significance of our approach in ensuring that interventions are implemented as intended, thereby enhancing the reliability and validity of our findings. Additionally, following statements from other systematics reviews (Watson et al., 2017; Infantes-Paniagua et al., 2021), PA patterns and active break intensity will be measured with objective instruments such as accelerometers or HR monitors (in both phases). On the other hand, several limitations warrant mention: (i) the generalizability of the results may be limited to our population context (encompassing factors such as primary school stage, socioeconomic status, etc.); (ii) resource constraints will necessitate the daily rotation of accelerometers among students during phase II.
